## Abstract

**Background:**

Up to 90% of people with multiple sclerosis (PwMS) subjectively report fatigue as one of their worst symptoms. Fatigability is an objectively measured component of fatigue. Cognitive fatigability (CF) is a breakdown in task performance following sustained cognitive effort. There is a paucity of interventions targeting CF in MS. The prior success of behavioural interventions at improving subjective fatigue suggests that their adaptation may yield similar results for CF. Given the relationship between CF, sleep quality, and mood, a behavioural intervention targeting these factors, such as cognitive behavioural therapy (CBT), is warranted. Given the multidimensional nature of fatigue, a multifaceted approach targeting lifestyle factors and coping (e.g., fatigue management education supplemented by CBT for insomnia and exercise) might prove efficacious.

**Aim:**

We describe a protocol for a pilot feasibility study to design and implement a multi-dimensional behavioural intervention to improve CF in PwMS.

**Methods:**

*Stage 1*: development of a multi-dimensional group-based videoconference-delivered behavioural intervention based on a previously successful fatigue management program for PwMS. A facilitator manual will be drafted. Course material will focus on four themes: body (sleep and physical activity), mood (impact of depression and anxiety), mind (cognitive contributions), and context (pacing and communication). *Stage 2*: a needs assessment survey will be completed by 100 PwMS for input on what factors are important contributors to their CF. Modifications will be made to the course material and manual. *Stage 3*: the facilitator-delivered intervention will include 20 PwMS. After baseline assessment, participants will attend weekly 70-min videoconference group sessions for 8 weeks, including homework assignments. Follow-up assessment will re-evaluate outcomes. *Stage 4*: analysis and dissemination of results. The primary outcome is improvement in CF. Additional feasibility outcomes will determine if a randomized control trial (RCT) is pursued. *Stage 5*: refine the intervention based on outcomes and feedback from participants. Determining which aspects participants felt were most effective will help inform RCT design.

**Conclusion:**

The long-term goal is to ensure that PwMS have access to effective interventions in real-world settings to improve quality of life and enhance their ability to participate in cognitively demanding activities that they enjoy.

## Introduction

Fatigue is one of the most commonly reported symptoms in MS, occurring in up to 90% of affected individuals (1, 2), with negative impacts on quality-of-life (3), self-esteem (4), and employability (5, 6). What is meant by the term fatigue varies throughout the literature. Definitions include a state of reduced capacity for work following a period of mental or physical activity (7), a feeling of physical tiredness and lack of energy that is distinct from sadness or weakness (8), extreme tiredness with the feeling that one needs to rest (9), a feeling of lack of energy, weariness, and aversion to effort (10), among other definitions (11). Fatigue has largely been regarded as a subjective experience unique to the individual, and thus it is typically measured by self-report. A number of questionnaires have been developed to that end, with some attempting to quantify fatigue and others evaluating the impact of fatigue on daily functioning, or both (12–17).

Given the disparate manner in which fatigue has been addressed in the literature, a unified taxonomy has been posited that distinguishes **fatigue** (i.e., an individual's subjective sensations) from **fatigability** (i.e., objective changes in performance) in order to provide clarification and consistency in both clinical and research applications (18, 19) (Figure 1). While there is a body of research that focuses on physical or motor fatigability (21), the focus of the current project is cognitive fatigability (CF) which can be operationally defined as *an inability to maintain optimal task performance throughout the duration of a sustained cognitive task* (7, 22, 23). Although fatigue is a well-studied concept in MS, CF is less well understood. While most studies measure fatigue using subjective self-report tools, fewer have measured objective CF. Given the negative impact of CF (24, 25), interventions are beginning to be introduced to address this concern, but the field is in its infancy.

**Figure 1 F1:**
[figure not shown]
Unified fatigue taxonomy. Fatigue classification. MRS, Modified Fatigue Impact Scale; MS, multiple sclerosis; FSMC, Fatigue Scale for Motoric and Cognitive Functions; WEIMuS, WuerzburiFatigue Inventory for Multiple Sclerosis; VAS, Visual Analogue Scale; NRS, Numerical Rating Scale; RT, reaction time (20).

Despite the nascent nature of the field, CF has been consistently demonstrated in MS through evidence of a breakdown in task performance across a variety of different cognitive tasks. Those with MS become more cognitively fatigued than healthy controls when performing information processing speed tasks, as reflected by a breakdown in their task accuracy (22, 23, 26). Similarly, reaction time increases over time more so for those with MS compared to controls on simple sustained attention tasks (27–29). Cognitive control (i.e., the combination of processes that allow adaptation of information processing depending on task goals) also declines over time in those with MS (30). Estimates of the frequency of CF is similar to the frequency of cognitive impairment in general in those with MS (31), with *1 in 2* meeting defined criteria for CF in two studies (32, 33).

Our group has extensively evaluated CF in MS. The current project is a natural extension of our work, which initially stemmed from listening to what was important to our patients from our clinical work. They told us that their ability to remain employed was negatively impacted by their susceptibility to fatigue. They noted that their cognitive performance waned as their day progressed but that their employers had little appreciation of this. Thus, it became our goal to find methods of objectively quantifying their experience of declining performance with sustained cognitive effort given that the self-report measures typically used did not capture their experience. Indeed, objectively measured CF does not typically correlate with subjective self-report measures of fatigue (23).

While CF can be evaluated in a number of different ways (34), our group has used the Paced Auditory Serial Addition Test (PASAT) as a measurement tool. Its sensitivity to CF differs depending on how it is scored (23, 26). When CF is evaluated longitudinally, it was found that the magnitude of CF does not change over time early in the disease course (35). Work in the field of CF has also recently been translated into clinical applications with the development of normative data to allow clinicians to determine whether the degree of CF experienced by their patients is statistically significant (36, 37).

Mechanisms of CF have been proposed, although studies vary regarding how CF is measured. CF has been associated with motor and processing speed, gender, and intelligence (33). Sleep quality, and to a lesser extent depression, have also been found to be predictors of CF in MS (38), although others found that the relationship between CF and sleep quality diminishes after controlling for depression (39). It has been postulated that impaired slow wave sleep may be causing the reduced sleep quality that contributes to CF and so treatments improving non-REM efficiency may be warranted (33). CF may also reflect brain-derived fatigue (i.e., directly related to pathological processes in the brain). In MS, this has been termed primary fatigue (40, 41). Disruptions in circuits involving the basal ganglia, frontal cortex, and thalamus have been implicated (42), and lesions in attention and arousal pathways, reticular and limbic systems and basal ganglia have been associated with CF (43, 44). Biomarkers of CF have also been identified in those with MS *via* functional neuroimaging, with differences in activation patterns in the attention network noted between those with MS and healthy controls before, during, and after a cognitively fatiguing task (29) and connectivity differences between those who subjectively report fatigue and those who do not (40). In addition to the influence of structural disease pathology, there are other biological variables such as inflammation that impact brain-derived central fatigue. Indeed, the influence of pro-inflammatory cytokines on fatigue has been demonstrated in MS (45).

There is an extensive literature addressing the treatment for subjectively evaluated fatigue in MS. These interventions generally stem from three different treatment approaches: pharmacological, procedural, and behavioural. *Pharmacological* treatments are often in the form of stimulants such as methylphenidate. The treatment is presumed to be effective given that it helps to overcome attentional difficulties and slowed processing speed, presumably due to its role as a dopamine agonist (46). Amantadine (antiviral), pemoline (stimulant) and modafinil have demonstrated positive results in treating subjective fatigue in those with MS. *Procedural* interventions include techniques such as light therapy, biofeedback, and neuromodulation. A recent review of the use of transcranial magnetic stimulation in MS found preliminary evidence of a beneficial impact on fatigue but replication in well-designed RCTs was recommended (47).

*Behavioural* approaches to treating fatigue have included a variety of methods including psychotherapy [i.e., cognitive behavioural therapy (CBT) or mindfulness], education/symptom management, cognitive rehabilitation and exercise (48, 49). CBT for insomnia (CBT-I) administered to those with MS has shown efficacy in improving insomnia, subjective fatigue and depression (50). A systematic review and meta-analysis on the utility of mindfulness training in the treatment of fatigue after stroke, TBI and MS concluded that these techniques were moderately effective (51). Another systematic review evaluating the efficacy of patient education programs at improving MS-related fatigue found that these programs had a positive effect, but they stressed the need for multidimensional approaches given that fatigue itself is a multidimensional symptom (52). Exercise training has also been explored as a potentially effective treatment and research in MS suggests that this approach is associated with a moderate reduction in fatigue symptoms (48, 53).

As noted above, while intereventions exist targeting subjective fatigue, our group's systematic review (54) highlighted the paucity of interventions specifically targeting objectively evaluated CF in MS. It is this gap in the literature that led to the current project. The presence of subjectively measured cognitive fatigue has been demonstrated to be predictive of MS disease progression in the form of relapses and brain atrophy (55). As such, early detection and treatment of CF may also have implications for disease course. If we can improve CF, then perhaps we can positively influence both quality-of-life and long-term disease outcomes. While procedural [i.e., transcranial direct current stimulation (tDCS)] (56) and pharmacological (i.e., Fampridine) (57) interventions have been recently studied, to date no behavioural interventions exist to improve CF. Given the negative impact of cognitive impairment (58) and fatigue (59) on quality-of-life, there is a need to find feasible and effective treatments to better the lives of those affected by MS. Although *no studies have yet addressed the impact of behavioural interventions on objective CF specifically*, the positive impact of these interventions on subjective fatigue can provide some direction in potentially fruitful options to pursue. Given the relationship between CF, sleep quality (39) and mood (38) a behavioural intervention designed to target sleep quality and mood, such as CBT, or more specifically CBT-I (50), may be warranted. However, as previously suggested, one must consider the multidimensional nature of fatigue when planning and designing treatment interventions and thus a multi-faceted approach targeting lifestyle factors and coping techniques (e.g., fatigue management education supplemented by elements of CBT-I and exercise) might have a greater chance of efficacy. A meta-analysis of exercise, education, and medication treatment interventions for fatigue noted that exercise interventions appeared to have stronger effects than medication given their ability to assist people with MS in coping with their existing disabilities beyond just symptom control (49), further supporting the inclusion of exercise training as a component of multimodal CF management. As such, this project provides a crucial first step towards establishing a multi-dimensional behavioural intervention as a feasible and effective tool to improve CF in those with MS and provides a foundation upon which to plan a future definitive RCT.

To summarize, in this protocol paper we report on the process of protocol development and the details for our behavioural intervention to target CF in people with MS (PwMS). This rationale stems from the well-developed literature outlining the development and administration of interventions to target fatigue in MS. Behavioural approaches have successfully reduced subjectively reported fatigue (52, 60) where pharmacological treatment of objective CF has shown little effect (57). Studies have demonstrated that CF can be influenced by other variables such as mood and sleep quality (38). There is the potential that additional variables, such as exercise, may also impact objective CF given the promising results observed with subjective fatigue and cognition (61). Through this accumulated evidence, the importance of addressing CF from a varied perspective has been established. The current project is a logical next step as the proposed behavioural intervention is designed to address CF using a multidimensional approach. The aims of the project we are reporting on here in this protocol paper are to develop, and pilot test (test the feasibility and preliminary efficacy of) a behavioural intervention designed to improve CF in persons with MS. In the current paper, we report on the process of protocol development, prior to actual implementation of the intervention. This will involve taking elements of already established fatigue management programs and adapting them to include treatment of factors that are known to contribute to CF (i.e., sleep quality, mood), as well as emerging treatments (i.e., exercise) expected to improve CF based on preliminary research. Clinical experience of the investigators and the perspectives of PwMS will also serve to inform the intervention's design.

## Materials and methods

We will apply for study approval through the Ottawa Health Sciences Network Research Ethics Board.

This is a pilot study that addresses questions of *feasibility* (i.e., whether something can be done, should we proceed with it, and if so, how), as well as a specific design feature where we test the *efficacy* of the intervention on a smaller scale in preparation for a future RCT (62). This project will proceed in five stages.

### Stage 1: Development

Stage 1 concerns the *development* of the multi-dimensional group-based behavioural intervention for CF. Pursuing behavioural treatment options is important given that they have the potential to be easily disseminated, can be made widely accessible, and have demonstrated efficacy at ameliorating secondary symptoms of MS (60). The intervention will be based on a previously successful teleconference-delivered fatigue management program for people with MS that was performed by our group (60). The current method of administration *via* videoconference was chosen given that it is easily accessible, does not require specialized technical support, as well as allowing more face-to-face interaction and therefore has the potential for wide dissemination. A videoconference-delivered program is also timely given that the COVID-19 pandemic has necessitated the need for healthcare professionals to find new and innovative ways of delivering healthcare remotely.

The foundations for the currently proposed program stem from a previously successful 6-week program designed to target *subjective fatigue*. This new intervention will be expanded to a tailored 8-week videoconference-delivered program. This expansion will allow for the incorporation of additional elements more specific to *objectively measured CF* based on findings from our group's systematic review (54), our research team's work in this area, and theoretical principles. For example, a prediction model of CF highlighted the impact of both mood and sleep quality (38). As such, elements of Cognitive Behavioural Therapy (CBT) and CBT for Insomnia (CBT-I) will be incorporated (in consultation with a Clinical Psychologist) as these have previously been shown to be effective at addressing both mood and sleep dysfunction in MS. Furthermore, although there is no work to date that addresses the impact of exercise on objective CF specifically, a meta-analysis demonstrated that exercise training is an effective intervention for reducing subjectively measured fatigue in MS (48) and benefits on cognition have also been documented (63). Therefore, the tailored program will incorporate a physical activity component. Once all elements are incorporated, a facilitator manual will be prepared to ensure that the standardized intervention can be reliably administered across different facilitators and locations. To address the multidimensional nature of CF, the course material will focus on four different themes: *body* (contributions of sleep and physical activity), *mood* (impact of depression and anxiety on fatigue), *mind* (cognitive contributions), and *context* (pacing, communication). See Figure 2 for the intervention components. For the specific content covered in each of the 8 sessions, see Table 1.

**Figure 2 F2:**
[figure not shown]
Intervention components.

**Table 1 T1:** Intervention session content.

Session #	Session content
1	Understanding cognitive fatigability
2	Prioritization and goal-setting
3	Physical activity
4	Sleep, rest and pacing
5	Managing your mood
6	Strategies for improving cognition
7	Managing contextual factors
8	Review session

### Stage 2: Needs assessment

Although the initial iteration of the intervention plan will be established based on previous research findings and clinical experience of the investigators, it is important to consider the input of PwMS directly to ensure that we prioritize factors that they deem to be important contributors to their own CF. As such, we will conduct a needs assessment survey.

A need can be defined as a gap between the current condition and a desired condition (64). Democratic needs are typically determined by the preferences of the majority and can be identified by surveying the target population (64). A needs assessment is a tool that can consider those who have a stake in a situation, help to clarify the issues, set future goals, and provide data to guide future decision-making (64). This approach to addressing gaps in care has been used successfully in the past to ensure that the needs of PwMS are considered when designing a model of care in an MS Clinic (65, 66). In the current circumstance, a needs assessment can help to ensure that the behavioural intervention being developed is one that is relevant and will address the CF needs of those individuals for whom it is designed. While there are many types of needs assessment, the one utilized here will be a *strategic needs assessment* (64) that will allow us to identify the gaps in current treatment for those PwMS impacted by CF.

The survey will include a brief demographic questionnaire to identify the characteristics of our sample. The survey will also include previously validated measures assessing fatigue, as well as cognition, mood, sleep quality and physical activity so that we can determine to what extent the individuals surveyed are impacted by these factors (factors identified in the literature to contribute to CF). We will also include items to identify what contextual factors influence the fatigue of those surveyed (e.g., family responsibilities, etc.), as previous work has identified that addressing such contextual factors is an important component of a multi-dimensional fatigue intervention (60). See Table 2 for a list of the outcome measures that will be administered as part of the needs assessment. The survey will then address how *disruptive* these various challenges are to the individuals surveyed and they will be asked to identify whether they feel these areas are *sufficiently addressed* in both the currently available health care and community support systems. If an area is identified as disruptive and insufficiently addressed, then this will constitute an identified need and will help guide refinements made to the intervention.

**Table 2 T2:** Questionnaires included in the needs assessment survey.

Area	Questionnaire
Fatigue	Modified Fatigue Impact Scale (77)
	Functional Assessment of Chronic Illness Therapy-Fatigue version (78)
	F-2-MS (78)
Cognition (self-report)	Perceived Deficits Questionnaire-5 (79)
Mood	Hospital Anxiety and Depression Scale (80)
Sleep Quality	Pittsburgh Sleep Quality Index (81)
Physical Activity	Godin Leisure Time Exercise Questionnaire (82)
Contextual Factors	Contextual Factors Affecting Functioning
Need Identification	Symptom Disruptiveness and Addressment Scale

We aim to survey a random sample of 100 PwMS. Following informed consent, respondents will be sent a secure link to a Qualtrics (67) survey that can be completed on a computer, tablet or smartphone at their convenience. Once data is compiled and analyzed, the information will inform potential modifications that may be needed to the proposed intervention plan. For example, if the survey were to reveal that contextual factors were less contributory to their CF than mood factors, then the intervention content addressing contextual factors could be diminished and the mood content could be further emphasized.

#### Data analysis for stage 2

Descriptive statistics will be compiled. We will determine what proportion of respondents rate the disruptiveness of each area of concern as high (i.e., they rate the degree of disruptiveness as a 4 or 5 on a Likert scale from 1 to 5). Similarly, we will determine what proportion of respondents rate the concern as being inadequately addressed (i.e., they rate the degree that the issues are addressed as 1 or 2 on a Likert scale from 1 to 5). This will then help inform how much emphasis should be given to each topic in the intervention. The more disruptive the issue and the less it is addressed with current resources, the greater emphasis it should have in the intervention. We will conduct a descriptive analysis to examine how those who indicate that CF is disruptive (i.e., 4 or 5 on the Likert scale) respond on questionnaires that reflect the themes covered in the intervention (i.e., mood, cognition, physical activity, context).

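### Stage 2 treats a need as disruptive and under-addressed together, but plans only the two separate proportions; sleep is also missing from one descriptive theme list

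*Protocol article*

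**What the plan says.** The protocol article, under Stage 2: Needs assessment, sets out what the survey is looking for: "If an area is identified as disruptive and insufficiently addressed, then this will constitute an identified need". The Discussion repeats the idea for persons: it expects every surveyed area to be flagged as both disruptive and currently unaddressed by some respondents.

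Under Data analysis for stage 2, two quantities are planned for each area. The first is the share scoring 4 or 5 on a five-point disruptiveness scale: "We will determine what proportion of respondents rate the disruptiveness of each area of concern as high". The second is the share scoring 1 or 2 on a five-point scale of how well the area is addressed: "Similarly, we will determine what proportion of respondents rate the concern as being inadequately addressed". Both are taken over all respondents. They are then combined in words: "The more disruptive the issue and the less it is addressed with current resources, the greater emphasis it should have in the intervention".

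A further descriptive analysis looks at respondents who rate cognitive fatigability (CF) as disruptive, and at how they "respond on questionnaires that reflect the themes covered in the intervention (i.e., mood, cognition, physical activity, context"). Sleep is not in that list. Under Stage 1: Development, the body theme covers "contributions of sleep and physical activity". Table 1 gives sleep a place in session 4, and Table 2 includes the Pittsburgh Sleep Quality Index (PSQI) in the survey.

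**The concern.** A need has two parts, and the survey records both for the same respondent and area. The stated analysis splits them. If those who find an area disruptive are mostly well served, while those who are not troubled by it rate it as poorly addressed, both shares can be high with few people in need. The reverse can also happen: moderate shares may come from one group that is both troubled and unserved.

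This is more than a curiosity here, because the survey aims at people with MS generally ("We aim to survey a random sample of 100 PwMS") and the article puts CF at about half of them. Respondents for whom an area is no problem therefore also enter the share calling it inadequately addressed. The results help decide how much weight each topic gets in the eight sessions before Stage 3 starts.

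The missing sleep entry is a smaller and separate matter. The list is introduced as if complete, so a literal reading leaves the PSQI out of the one stated Stage 2 analysis restricted to respondents troubled by CF.

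**Working it through.** The document gives no expected proportions and no precision or power figure for Stage 2, so there is no stated number to reproduce. The check asks what the two planned proportions can reveal about the joint one.

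**Inputs.** n = 100 (Stage 2). Let d be the share rating an area 4–5 on disruptiveness and u the share rating it 1–2 on being addressed. All values of d and u below are assumptions.

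**Formula.** For the share J holding both ratings, the Fréchet bounds are max(0, d + u − 1) ≤ J ≤ min(d, u). If the ratings are independent, J = d × u.

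| d | u | Lowest J | J if independent | Highest J |
|---|---|---|---|---|
| 30% | 30% | 0% | 9% | 30% |
| 50% | 50% | 0% | 25% | 50% |
| 60% | 50% | 10% | 30% | 50% |
| 60% | 60% | 20% | 36% | 60% |
| 70% | 40% | 10% | 28% | 40% |
| 70% | 70% | 40% | 49% | 70% |
| 80% | 80% | 60% | 64% | 80% |

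**Can the order change?** Take area A at 60%/60% and area B at 50%/50%. Both separate shares favour A. At the extremes, A may have 20 of 100 respondents with both ratings (40 disruptive only, 40 under-addressed only, 0 neither), while B has 50 of 100 (50 both, 50 neither).

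A reversal does not need both extremes. If the ratings are independent in A (J = 36%), B overtakes once its J exceeds 36%. The correlation between the two yes/no ratings in B is then (0.36 − 0.25) / 0.25 = 0.44. So the association must differ clearly between areas. If the ratings are independent in both, A keeps its lead (36% against 25%).

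**Does the verbal rule always give an order?** No. It ranks A above B only if A is at least as high on both shares. Between 70%/40% and 60%/50% it is silent.

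**Can the Discussion's expectation be checked?** The lower bound exceeds zero only if d + u > 100%. For any area below that, the two proportions cannot show that even one respondent holds both ratings.

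**Precision of the joint share.** The half-width of a 95% interval is 1.96 × √(J(1 − J)/n). At J = 25% and n = 100 it is 1.96 × √(0.1875/100) = 8.5 points. If half of the respondents rate CF as disruptive (an assumption, n = 50), it is 1.96 × √(0.1875/50) = 12.0 points.

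**Sleep.** No arithmetic applies. Set side by side, the Stage 1 body theme, session 4 in Table 1 and the PSQI in Table 2 all include sleep; the theme list closing the Stage 2 analysis does not.

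**The case against.** The strongest reply is that the definition is worded for an area, not a respondent. Stage 2 also draws on a majority-preference notion of need, under which one proportion per dimension per area is a fair summary. The analysis brings the two together through its emphasis rule, and says only that the result helps inform emphasis. There is no mechanical ranking to go wrong. The wide gaps in the table are limits on assumed inputs, and they narrow when both shares are high (60% to 80% at 80%/80%). The article is a condensed account, and cross-tabulations and interval methods are often left to a fuller plan.

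Much of this stands. The area wording means that the two sections do not flatly contradict each other, and an area high on both shares will often be a real need. Two things remain. The Discussion speaks of individuals indicating both, which the separate shares often cannot confirm. And the article does fix the cut-offs, the proportions and the combining rule, so this is a comment on a stated method rather than on a missing detail.

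On sleep, the reply is largely right. The two proportions are planned for each area of concern, nothing there excludes sleep, and Stage 2 names sleep quality among the factors surveyed. Nor should the point lean on sleep being the stronger predictor of CF: the Introduction reports that finding, but also that others saw the association diminish after controlling for depression.

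**Conclusion.** The point holds in a limited form. The two planned proportions are relevant to need but do not determine how many respondents find an area both disruptive and under-addressed. The joint share can range over 0–50% at assumed shares of 50%/50% and 20–60% at 60%/60%, so topics can order differently by separate shares than by unmet need. Whether they would do so in this survey is unknown: it depends on how the association between the ratings varies across areas, for which the document gives no data.

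A reader might infer that the tailoring rests on a wrong quantity, or that sleep has been dropped from it. The document supports neither. The need is defined at area level, both shares are used together and only to inform judgement, and the per-area proportions are not said to exclude sleep. The sleep omission is a drafting inconsistency confined to the separate description of respondents with disruptive CF.

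Stage 2 is descriptive, so no error rate or sample size is affected. What is at stake is how well the survey guides session content.

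**What to change.** In Data analysis for stage 2, add for each area the proportion of respondents who rate disruptiveness 4–5 and addressed 1–2 together, with a 95% confidence interval, overall and among those rating CF as disruptive. State that it will be considered alongside the two separate proportions when topic emphasis is set. Add sleep (PSQI) to the theme list in the last sentence of that section.

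The cost is one cross-tabulation per area of ratings already being collected, plus a few words of text. The survey needs no new items or respondents. Intervals in the subgroup with disruptive CF will be somewhat wider than in the whole sample, which should be borne in mind when areas are close.
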